
## Ethical considerations

### Regulation statement

The PANDORINA trial will be conducted according to the principles of the Declaration of Helsinki (64th version, October 2013) and in accordance with the local laws and regulations, such as in the Netherlands the Medical Research Involving Human Subjects Act. The local principal investigator is responsible for making sure that local laws and regulations are followed.

### Recruitment and consent

All subjects will be recruited at the outpatient clinic by one of the principal investigators. The principal investigator may be replaced by an assigned substitute, who is fully informed and aware of the study requirements and procedures, e.g., the study coordinator, local treating physician, or a study nurse. The approached patient will be given at least 24 hours’ time to consider informed consent and to make a decision. If indicated, surgery will be performed within 4 weeks after determination of the diagnosis, so there is sufficient time for explanation of the disease severity. Furthermore, due to this the patient will have sufficient time to explain her/his prospects and to consider the (dis)advantages of participating in the study. Participant retention and complete follow-up was promoted by periodic meetings and site visits with outcome data and corresponding time windows.

### Objections by minors or incapacitated subjects

Minors and incapacitated patients will not be included in this study.

### Benefits and risks assessment group

Prophylactic abdominal drainage can be useful for early detection of pancreatic juice in case of a POPF but drains might themselves also contribute to these complications. Patients will not undergo additional investigations and interventions due to participation in the PANDORINA trial and therefore risks to subjects involved in this trial are similar to every other patient undergoing DP in routine clinical practice, especially since the Van Buren multicenter RCT already demonstrated the safety of omitting prophylactic abdominal drainage. Potential benefits for subjects in the investigational treatment arm could be fewer major complications, less abdominal pain, and less discomfort in case of no prophylactic drainage.

## Discussion

PANDORINA is the first binational, multicenter, randomized controlled non-inferiority trial with the primary objective to evaluate the hypothesis that omitting prophylactic abdominal drainage after DP does not worsen the risk of postoperative severe complications [18, 19]. The focus of this study is to assess if operative placed drains lead to less complicated POPF which need a reintervention or reoperation. However, POPF B/C without intervention cannot be measured in the no drain arm of our study since this is because of prolonged operative drainage. Therefore, the primary endpoint is chosen to be severe morbidity, while this is caused by a POPF grade B/C, on which the clinical focus will lie. Most of the published studies on drain placement after pancreatectomy focus on both pancreatoduodenectomy and DP, but these two entities present are associated with different complications and therefore deserve separate evaluation [29, 30]. The PANDORINA trial is innovative since it takes the preoperative risk on POPF into account based on the D-FRS and it warrants homogenous stump closing by using the same graded compression technique and same stapling devive [22, 24].

Several studies provide better insight into the value of abdominal drainage after PD. In a cohort of 69 patients after DP (39 with and 30 without a drain), Paulus et al. [31] did not observe a decrease in the incidence of intra-abdominal abscess, POPF [32], or pseudocyst formation in case of intra-abdominal drainage. In a randomized trial by Conlon et al [1] in 179 patients undergoing pancreatic resection (among them 40 distal pancreatectomies), no benefit was seen for prophylactic abdominal drainage*.* However, the statistical analysis was conducted without distinction between pancreatoduodenectomy and DP. Behrman et al. [6] used propensity scored matching to compare 706 patients undergoing DP with or without prophylactic abdominal drainage. They observed a higher incidence of POPF in those patients who received drains; however, their analysis included the clinically non-relevant POPF Grade A [33].

A randomized trial by Bassi et al. reported the outcome of early vs late removal of the intra-abdominal drain after pancreatectomy in 114 patients of whom 39 underwent DP [33]. They found an increase incidence of POPF, intra-abdominal infected collections, pulmonary complications, length of stay (LOS), and readmission in the group of late drain removal. They concluded that late drain removal is a risk factor for POPF. This finding was confirmed in a recent study by Seykora et al. in which in 5581 DPs (POPF grade B/C rate 17%) early drain removal (in 716 patients) was associated with improved outcomes [34].

Recently, Van Buren et al. reported the first multicenter randomized controlled trial in 344 patients undergoing DP with (*n*=174) and without (*n*=170) prophylactic intra-abdominal drainage [2]. Their hypothesis was that DP without routine intra-abdominal drainage does not affect the frequency of grade 2 or higher-grade complication (according to the Common Terminology Criteria for Adverse Event [23]). The rate of grade 2 complications was comparable between the groups (44% vs. 42%, *p*=0.80). The rate of grade B/C POPF did not differ and was 6% lower in the group without abdominal drainage (18% vs 12%, *p*=0.11) either. This led to the conclusion that clinical outcomes after DP with or without drain are comparable. The Van Buren trial does not describe a standardized technique of pancreatic stump closure and does not stratify patients to their risk of POPF after DP.

[name] et al. described the now commonly used graded compression technique for DP [17, 24]. By compressing the pancreatic tissue gradually based on the experienced resistance, the pancreatic parenchyma is compressed rather than crushed before transecting, which results in low rates of POPF [17]. A reduction in POPF using this technique was confirmed in two other studies, one study showed that out of 42 patients undergoing DP, 17 were treated with the graded compression technique and did not develop POPF (0%) compared to 28% of the patients in the comparison group [35, 36]. The intra-abdominal drainage period and the median LOS were significantly shorter in the graded compression group compared to the no-graded compression group.

In order to assess the rationale of prophylactic abdominal drainage after DP, we designed a binational multicenter randomized control trial (RCT). All patients undergoing DP with open and minimally invasive techniques (laparoscopic and robotic), with and without preservation of the spleen, are eligible for the study.

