## Abstract

**Background:**

Prophylactic abdominal drainage is current standard practice after distal pancreatectomy (DP), with the aim to divert pancreatic fluid in case of a postoperative pancreatic fistula (POPF) aimed to prevent further complications as bleeding. Whereas POPF after pancreatoduodenectomy, by definition, involves infection due to anastomotic dehiscence, a POPF after DP is essentially sterile since the bowel is not opened and no anastomoses are created. Routine drainage after DP could potentially be omitted and this could even be beneficial because of the hypothetical prevention of drain-induced infections (Fisher, Surgery 52:205–22, 2018). Abdominal drainage, moreover, should only be performed if it provides additional safety or comfort to the patient. In clinical practice, drains cause clear discomfort. One multicenter randomized controlled trial confirmed the safety of omitting abdominal drainage but did not stratify patients according to their risk of POPF and did not describe a standardized strategy for pancreatic transection. Therefore, a large pragmatic multicenter randomized controlled trial is required, with prespecified POPF risk groups and a homogeneous method of stump closure.

The objective of the PANDORINA trial is to evaluate the non-inferiority of omitting routine intra-abdominal drainage after DP on postoperative morbidity (Clavien-Dindo score ≥ 3), and, secondarily, POPF grade B/C.

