### Sample size calculation

The PANDORINA trial is as a non-inferiority randomized trial, hypothesizing that the outcome (i.e., postoperative complications Clavien-Dindo score ≥ 3 and, secondarily, clinically relevant POPF, grades B and C) in patients undergoing DP without prophylactic abdominal drainage are non-inferior to those of patients with routine prophylactic abdominal drainage after surgery. The sample size is calculated according to the formula (available at https://www.sealedenvelope.com/power/binary-noninferior/):$$n=f\left(\alpha, \beta \right)\times \left[{\pi}_{\mathrm{s}}\times \left(100-{\pi}_{\mathrm{s}}\right)+{\pi}_{\mathrm{e}}\times \left(100-{\pi}_{\mathrm{e}}\right)\right]/{\left({\pi}_{\mathrm{s}}-{\pi}_{\mathrm{e}}-d\right)}^2$$ where *π*_s_ and *π*_e_ are the true percent “success” in the “drain” and “no drain” groups respectively.$$F\left(\alpha, \beta \right)={\left[{\varPhi}^{-1}\left(\alpha \right)+{\varPhi}^{-1}\left(\beta \right)\right]}^2$$

And *φ*^−1^ is the cumulative distribution function of a standardized normal deviate.

Patients recruited in the PANDORINA trial will be randomized within the referred Institute with a 1:1 allocation ratio. The primary endpoint of the present trial is the rate of Clavien-Dindo ≥3 major complications, following the assumption: 2.5% one-sided significance level (*α*), 80% power (1−*β*), and a non-inferiority level of 8%. The expected success percentage in the intervention arm (no prophylactic abdominal drainage) of 77% and a success percentage in the control group of 70% (prophylactic abdominal drainage, based on the multicenter LEOPARD trial with a majority of minimally invasive procedures) [21]. The needed number of patients was calculated with a sealed envelope: a total of 272 patients are required. Including a 3% of possible drop-out after randomization, the total required sample size is 282 patients (141 patients per arm).

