The most relevant secondary endpoint is the rate of clinically relevant POPF (grades B and C). The sample size was calculated with the following assumption: 2.5% one-sided significance level (*α*), 80% power (1−*β*), and a non-inferiority level of 8%. The expected success percentage in the intervention arm (no prophylactic abdominal drainage) is 81%, and a success percentage in the control group (prophylactic abdominal drainage) is 75%. This difference of 6% less grade B/C POPF without abdominal drainage is based on the Van Buren trial, and the baseline risk of 25% grade B/C POPF is based on the recently published distal fistula risk score (D-FRS), a combined Dutch/Verona multicenter study [22]. The needed number of patients was calculated with sealed envelope: a total of 274 patients. Including a 3% of possible drop-out after randomization, the total required sample size is 282 patients (141 patients per arm).

Based on the second (slightly lager) sample size calculation, we will include 282 patients so that conclusions can be drawn for both endpoints.

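### POPF grade B/C is sized for a non-inferiority conclusion, yet the protocol says part of it cannot be measured in the no-drain arm, which tilts that secondary comparison toward non-inferiority

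*Protocol article*

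**What the plan says.** The objective in the Abstract is non-inferiority "on postoperative morbidity (Clavien-Dindo score ≥ 3), and, secondarily, POPF grade B/C". The hypothesis under Sample size calculation repeats this for Clavien-Dindo 3 or higher and, "secondarily, clinically relevant POPF, grades B and C".

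The same section says: "The most relevant secondary endpoint is the rate of clinically relevant POPF (grades B and C"). It gives this endpoint its own calculation, with a "2.5% one-sided significance level", 80% power and "a non-inferiority level of 8"%. The assumed success rates are ("no prophylactic abdominal drainage) is 81%, and a success percentage in the control group (prophylactic abdominal drainage) is 75"%. The result is 274 patients, or 282 with drop-out. This calculation, slightly larger than the one for the primary endpoint, fixes the final size, and the stated reason is that "we will include 282 patients so that conclusions can be drawn for both endpoints".

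The Definitions section applies one ISGPS grade B/C definition to both arms. Nothing in the article limits the POPF endpoint to events that both arms can register.

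The Discussion then says that "POPF B/C without intervention cannot be measured in the no drain arm of our study since this is because of prolonged operative drainage" and gives this as the reason why severe morbidity was made primary.

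**The concern.** The authors considered the measurement problem serious enough to keep POPF from being the primary endpoint. The same endpoint, unmodified, still carries a non-inferiority hypothesis, a margin, an error rate and a power claim, and it determines the final sample size.

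A drain-arm patient can become a grade B/C case because an operative drain stays in for long. A no-drain patient almost never can. The mechanism is in the article: under Prophylactic abdominal drainage, drain-arm drains may stay beyond day 3 when amylase, volume or fluid aspect meets the stated criteria.

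The extra cases raise the control rate, so the error runs in one direction and favours the claim under test. A finding that POPF is no worse without a drain could then partly reflect what each arm is able to record. Blinded adjudication (Statistical analysis) does not help, because it checks events against the definitions and the asymmetry lies in the definition.

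**Working it through.** **Inputs** (Sample size calculation): success 75% with drain and 81% without, so POPF B/C 25% and 19%; margin 8 points; one-sided alpha 2.5%; power 80%.

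**The plan's own figure.** n per arm = (1.96 + 0.8416)² × [75×25 + 81×19] / (75 − 81 − 8)² = 7.849 × 3414 / 196 = 136.7, so 137 per arm and 274 in total. This matches. Drop-out: 274 / 0.97 = 282.5, against 282 stated, a rounding matter. The arithmetic is sound; the difficulty lies in the endpoint.

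**Effect of unequal measurement.** With observed POPF rates pC (drain) and pN (no drain) and n = 137 per arm:

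P(declare non-inferiority) = Φ( [0.08 − (pN − pC)] / SE − 1.96 ), with SE = √{[pC(1−pC) + pN(1−pN)] / 137}.

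The share of grade B/C due only to prolonged drainage is not in the documents. Every value of it below is an assumption.

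*(a) Fixed points.* Controls show 25%, of which b points are drainage-only. Comparable fistulas are truly 8 points more frequent without a drain, so pN = 0.25 − b + 0.08.

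| b (points) | pN | SE | P(false non-inferiority) |
|---|---|---|---|
| 0 | 0.33 | – | 2.5% |
| 2 | 0.31 | 0.0541 | 5.6% |
| 4 | 0.29 | 0.0536 | 11.2% |
| 6 | 0.27 | 0.0530 | 20.4% |
| 8 | 0.25 | 0.0523 | 33.3% |

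*(b) Proportional loss.* The true no-drain risk is 33%, and a fraction f of those events goes unclassified, so pN = 0.33 × (1 − f). P(false non-inferiority) is 8.9% at f = 10%, 23.9% at 20% and 48.3% at 30%. At similar shares the two models differ (8 of 25 points is 32% and gives 33%; f = 30% gives 48%). The direction is therefore firm and the size depends on the model.

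*(c) Equal true risks of 25%.* A loss of f = 24% gives pN = 0.25 × 0.76 = 0.19, exactly the planned 19% versus 25%. P(declare non-inferiority) is then 80%, against 33% with no loss.

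**A restricted endpoint at the present size.** If only POPF requiring intervention or grade C is counted and the arms truly do not differ, power at 137 per arm is 39% at 19% in both arms and 52% at 12.5% in both arms (rates assumed). For 80% power the totals would be 756 and 538.

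**The case against.** Several points on the other side stand.

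- The Discussion discloses the limitation and acts on it. Severe morbidity is primary, and a fistula graded B/C without any intervention does not by that alone become a Clavien-Dindo 3 event. A reader might infer that the trial's main non-inferiority conclusion is biased; the documents do not support that.
- A reader might also infer that these fistulas cannot occur without a drain. The text says only that they cannot be measured, and the section on prophylactic drainage provides for no-drain patients who receive a drain despite randomization. The exclusion is near-complete, not absolute.
- Statistical analysis names a non-inferiority test for the primary endpoint only. For POPF, the intention rests on the objective, the hypothesis, the sizing and the statement about both endpoints. Those are still enough to fix an intended conclusion.
- Part of the difference may be real. Clinical background says that a leak without a drain may remain a sterile, asymptomatic pseudocyst needing no intervention. Prolonged drainage would then be a burden of the drain strategy and not only a labelling effect. This is a fair reading of a strategy comparison, but the Discussion presents the matter as one of measurement, and the article does not define the POPF endpoint as drain burden.
- The planned 6-point advantage comes from an earlier drain versus no-drain trial (18% versus 12%, p = 0.11). The same asymmetry may have contributed there, but nothing in the documents shows that it did.

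**Conclusion.** The contradiction is in the text. Unmodified POPF B/C cannot carry the non-inferiority conclusion that the sample size section claims for it while the Discussion says that part of it is not measurable in one arm. The direction, toward non-inferiority, follows from the article itself.

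The magnitude does not. The range of about 6% to 33% false non-inferiority rests on assumed shares of 2 to 8 of the 25 control points, on a true excess at the margin, and on a normal approximation with 137 per arm. The tempting stronger statement is that the planned 6-point benefit is purely a product of the definition. Calculation (c) shows this to be possible, at a 24% loss, but the documents give no share that would make it more than a possibility. The point is limited to the POPF comparison.

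**What to change.** Reconcile Sample size calculation with the Discussion, before database lock:

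1. Withdraw or qualify, for unmodified POPF B/C, the statement that conclusions can be drawn for both endpoints.
2. Report full ISGPS B/C by arm descriptively, with cases graded only for prolonged operative drainage shown separately.
3. Add a prespecified comparison of POPF requiring intervention or grade C, labelled supportive. Postoperative interventions, their reasons and days with a drain are already listed under Secondary parameters/endpoint, so no new data items should be needed.

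**Cost.** The text change is small, but POPF loses its stated 80%-power non-inferiority claim. The restricted comparison does not replace it: its event rate is lower, and with no true difference its power is only about 39% to 52% under the assumed rates. The totals of 538 to 756 needed for 80% power are far above the planned 282, of which 152 had been randomized at submission (Trial status). It also overlaps with the primary endpoint. And it may tilt the other way, because a leak drained percutaneously in the no-drain arm would count while the same leak controlled by an operative drain would not. For these reasons it should be supportive and not confirmatory, and read beside the descriptive table.

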## Conclusion

PANDORINA is a binational multicenter, randomized controlled non-inferiority trial with the primary objective to evaluate that omitting prophylactic abdominal drainage after DP does not worsen the risk of postoperative Clavien-Dindo score ≥ 3 complications [18, 19]. Additional to the current literature, the PANDORINA trial makes prespecified fistula risk groups and guarantees homogenous stump closure.

### Trial status

Confirmation of funding of the trial by Ethicon UK (Johnson & Johnson Medical Limited, Edinburgh, UK) was received on September 25, 2017. Ethical approval in the Amsterdam UMC was received on September 25, 2020. The PANDORINA trial was registered in the Netherlands Trial Register on December 11, 2020 (NL9116). The first patient was randomized on November 02, 2020. At the time of submitting this protocol for publication (May 4, 2022), all centers were actively recruiting patients for the trial and 152 out of 282 (54%) have been randomized, which means that inclusion is on schedule.

## Data Availability

Data will be available to the study coordinators. All publications and presentation using this data will be approved by all authors.
